#### Sample size calculation

The study has been designed as a pilot study aiming to enroll at least 24 patients. After the enrollment of a predefined group of participants, an interim analysis will be performed to define a desirable group of patients needed to evaluate the aforementioned study outcomes.

### Statistical analysis

Statistical analysis of all data obtained throughout the study period will be performed. Initially, baseline population characteristics will be analyzed to evaluate potential imbalances between study arms. Data obtained from at least 24 consecutive participants will be processed using appropriate statistical models to evaluate findings regarding study primary and secondary outcomes. Main statistical analyses will be performed using analysis of variance (ANOVA) repeated measures with time effect and placebo-drug effect (right versus left side of the body). The statistical significance of differences between groups will be estimated using analysis of contrasts.

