## Methods

### Design

The study has been designed as a single-center, randomized, double-blind, placebo-controlled pilot trial. The study period has been set between October and March to eliminate any potential positive influence of sunlight on vitiligous lesion repigmentation. Recruitment started on 1 December 2016. The study end date is anticipated to be 30 April 2019. The study population will comprise patients with the NSV acrofacial active form of vitiligo. Upper and lower limb involvement is an obligatory inclusion criterion in screened patients. A total number of at least 24 enrolled patients is planned for the study. All enrolled participants will apply ointment including 1% simvastatin-acid sodium salt onto a preselected limb and vehicle ointment onto an opposite limb and 1% atorvastatin calcium salt ointment onto another preselected limb and vehicle ointment onto an opposite limb, taking into account different combinations as presented in Fig. 1. Such a scheme of ointment administration allows a direct comparison of the effects of active substance and placebo due to the identical biological model and a similar area of vitiligous lesions.

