#### Intervention

All enrolled patients will receive four containers with the following ointments: 1% simvastatin-acid sodium salt, 1% atorvastatin calcium salt, and two vehicle ointment-filled containers labeled with a preselected limb as follows: “left upper limb”, “right upper limb”, “left lower limb”, and “right lower limb”. In each case, application of an active substance to a particular limb is associated with application of the vehicle ointment onto the opposite limb as previously described. The exact description of the randomization process is presented below.

Study participants will apply ointments twice daily (every 12 h) according to the container labels. An approximate amount of 1 cm of ointment is advised for palm-sized lesions. Study drugs must be stored at room temperature.

During the study period, participants are not allowed to initiate treatment with systemic statins due to any other medical conditions. In case of a necessity to start statin uptake during the study period, the patient’s participation will be prematurely terminated. Moreover, administration of any other topical active substances on lesional areas is forbidden throughout the study period. The systemic use of any immunosuppressive or immunomodulating medications, as well as laser therapy or phototherapy, is not allowed throughout the study.

Participants are not allowed to use any other additional vitiligo treatment, either systemic or topical, including the use of antioxidants, *Ginkgo biloba*, or dermocosmetics.

The study period was defined as 12 weeks. The visit schedule includes a screening visit, when all necessary data including blood sample results will be gathered, baseline (week 0) and three evaluation visits every 4 weeks (week 4, week 8, and week 12). During each visit all participants will be provided with a new set of previously weighed study drugs. Previously distributed containers need to be returned at each visit, and their final weight will be recorded in the study documentation after return. Photographic documentation of vitiligous lesions will be recorded during each visit.

Sunbathing is prohibited throughout the whole study period.

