#### Randomization and blinding

Randomization of study participants into the arms was performed using Random Allocation Software version 1.0. The study was designed as a double-blind trial. The preparation of study drugs, as well as the process of blinding, was performed by the Department of Pharmaceutical Technology, Nicolaus Copernicus University, Faculty of Pharmacy in Bydgoszcz. The study drugs are delivered in identical containers labeled with the consecutive participant number and an assigned application area, i.e., “left upper limb”, “right upper limb”, “left lower limb”, or “right lower limb”. The weight of all containers is identical at the moment of delivery. Organoleptic properties, including color, consistency, tenacity, and smell of the studied ointments are highly similar, thus making the substances indistinguishable for both participant and investigator.

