#### Secondary outcomes

Secondary outcomes of the study comprise safety and tolerability of the study drugs, assessed as the number of participants with treatment-related adverse events according to Common Terminology Criteria for Adverse Events (CTCAE) version 4.0, the percentage of patients who achieved particular response rates (none, 0%; poor, 1–25%; moderate, 26–50%; good, 51–75%; excellent, > 75%) in each arm assessed as a relative reduction in lesional skin area, as well as with the BSA and VASI scale, a comparison of simvastatin and atorvastatin efficacy between study participants, the association between disease duration and repigmentation rate in the study arms, and the association between estimated daily ointment use (grams per square centimeter of skin) and the repigmentation rate in study arms.

The complete list of study outcomes is presented in Table 2.

**Table 2 Tab2:** A complete list of the EVRAAS study outcomes

Primary outcome	Secondary outcomes
1. Evaluation of repigmentation of vitiligous lesions achieved after the administration of 1% simvastatin-acid sodium salt or 1% atorvastatin calcium salt ointments compared with vehicle ointment after a 12-week study period (change from baseline in repigmentation on BSA and VASI scale).	1. Number of participants with treatment-related adverse events as assessed by CTCAE version 4.0 2. Percentage of patients who achieved particular response rate in each arm assessed as a relative reduction in lesional skin area as follows: none, 0%; poor, 1–25%; moderate, 26–50%; good, 51–75%; excellent, > 75% 3. Percentage of patients who achieved particular response rate in each arm assessed as a relative reduction in BSA scale as follows: none, 0%; poor, 1–25%; moderate, 26–50%; good, 51–75%; excellent, > 75% 4. Percentage of patients who achieved particular response rate in each arm assessed as a relative reduction in VASI scale as follows: none, 0%; poor, 1–25%; moderate, 26–50%; good, 51–75%; excellent, > 75% 5. Comparison of simvastatin and atorvastatin efficacy between study participants 6. The association between disease duration and repigmentation rate in study arms 7. The association between estimated daily ointment use (grams per square centimeter of skin) and repigmentation rate in study arms

*BSA* body surface area, *CTCAE* Common Terminology Criteria for Adverse Events, *VASI* Vitiligo Area Scoring Index

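### Each limb's week-0 lesion extent is measured but is not a covariate in the stated repeated-measures ANOVA; adjusting for it and using all available visits would sharpen a valid paired comparison

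*Protocol article*

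**What the plan says.** All references are to the protocol article.

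- **Design of the comparison.** The Intervention section states "All enrolled patients will receive four containers with the following ointments" and lists one simvastatin, one atorvastatin and two vehicle ointments, one per limb. It adds that "application of an active substance to a particular limb is associated with application of the vehicle ointment onto the opposite limb".
- **Why the limbs are held to be comparable.** The Design section says the scheme permits a direct comparison "due to the identical biological model and a similar area of vitiligous lesions". Table 1 contains no criterion requiring similar lesion extent on the two sides.
- **What is measured.** Lesion area is obtained by planimetry from photographs at every visit, week 0 included.
- **Primary outcome.** Table 2 defines it as "change from baseline in repigmentation on BSA and VASI scale" at 12 weeks.
- **Analysis.** The Statistical analysis section first says that "baseline population characteristics will be analyzed to evaluate potential imbalances between study arms". The main model is "analysis of variance (ANOVA) repeated measures with time effect and placebo-drug effect (right versus left side of the body"), followed by contrasts. No baseline covariate is named.
- **Incomplete follow-up.** The Intervention section foresees it: "In case of a necessity to start statin uptake during the study period, the patient’s participation will be prematurely terminated". No dropout rate is given.

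**The concern.** A comparison of participant characteristics between arms belongs to a parallel-group trial. Here the simvastatin, atorvastatin and vehicle limbs belong to the same people, so age, sex or disease duration cannot differ between treatments. What can differ by chance is how much lesion each limb carries at the start. The plan relies on left-right similarity, does not require it, measures it, and then leaves it out of the named model.

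Classical repeated-measures ANOVA also needs a full set of visits from each participant, unless something is done about missing values.

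At stake are the precision of a trial planned for at least 24 participants, and how far its estimate follows a chance baseline difference. The Sample size calculation section uses these data in an interim analysis to set the number of patients needed, so avoidable noise would carry into that number.

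**Working it through.** The plan gives no significance level, power, effect size, standard deviation or dropout rate, so its figure of 24 cannot be reproduced. The correlations and missing-visit rates below are assumptions.

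**1. The baseline check.** Each participant contributes one limb or more to every treatment. Any person-level characteristic therefore differs between treatments by exactly 0. Only limb-level quantities, such as lesion extent, can differ.

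**2. Precision.** Take the active-minus-vehicle limb difference, scaled to variance 1 at week 0 and at week 12, with correlation rho between the two.

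- Change-score variance: 2(1 - rho).
- Baseline-adjusted variance: 1 - rho².
- Ratio, adjusted to change score: (1 + rho)/2.
- Participants needed by the change score relative to adjustment: 2/(1 + rho).

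| rho (assumed) | Change score | Adjusted | Ratio | Extra participants for change score |
|---|---|---|---|---|
| 0.5 | 1.00 | 0.75 | 0.75 | 33% |
| 0.7 | 0.60 | 0.51 | 0.85 | 18% |
| 0.9 | 0.20 | 0.19 | 0.95 | 5% |

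**3. Check at n = 24.** These are 20,000 simulated trials per rho, with no treatment effect and one pair of limbs per participant. The variance ratio is the square of adjusted SE over change-score SE.

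| rho | SE, change | SE, adjusted | Variance ratio | Type I error, change | Shift in change estimate per unit of mean baseline difference |
|---|---|---|---|---|---|
| 0.5 | 0.2025 | 0.1796 | 0.79 | 0.049 | -0.49 |
| 0.7 | 0.1579 | 0.1489 | 0.89 | 0.049 | -0.30 |
| 0.9 | 0.0917 | 0.0914 | 0.99 | 0.047 | -0.10 |

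The change-score test holds its 5% level. Its estimate still moves with the chance baseline difference by about -(1 - rho) per unit, and adjustment removes that movement. Estimating the slope from 24 pairs uses up part of the gain: the ratios are slightly worse than the formula gives, and at rho = 0.9 almost nothing is gained.

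**4. Missed visits.** Let q be the chance of missing each of the three follow-up visits, independently.

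- Complete at all three: (1 - q)³ = 0.857 for q = 0.05 and 0.729 for q = 0.10. Of 24 participants, 20.6 and 17.5 remain.
- With a week-12 value: 1 - q = 0.95 and 0.90.
- Avoidable SE excess of complete cases over everyone with a week-12 value: sqrt(0.95/0.857) = 1.05 and sqrt(0.90/0.729) = 1.11, that is 5% and 11%.

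**The case against.** **Baseline is already used.** This stands. The primary outcome subtracts it, and week 0 may also be a level of the time factor. A reader might infer that starting differences make the test invalid; the simulated type I error of 0.047 to 0.049 shows otherwise. A reader might also compare adjustment with an unadjusted week-12 contrast, where the variance ratio 1 - rho² falls to 0.51 or 0.19 at rho 0.7 or 0.9. The plan does not propose that contrast, so those larger gains do not apply.

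**Arms may not mean treatments.** The Randomization and blinding section says "Randomization of study participants into the arms was performed using Random Allocation Software version 1.0", and Fig. 1, which is not shown, presents different limb combinations. If arms are those combinations, participant characteristics can differ between them. Baseline characteristics might also include lesion extent. Both readings are open, so the check is uninformative only on the treatment reading. It is descriptive and changes no estimate either way.

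**Missing-data rules are usually left to a fuller document.** This also stands: the article states no complete-case restriction. The loss in step 4 is a conditional consequence of the classical method, not a stated error. A reader might quote an SE increase of 8-17% (1/sqrt(0.857) = 1.08 and 1/sqrt(0.729) = 1.17). That compares with no missing data at all, which no model can deliver. Participants terminated for starting a statin will typically have no week-12 value under any model; for them, earlier visits add only indirect information.

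What survives is that the article does name a specific main model, and a measured variable directly relevant to the paired contrast is not in it.

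**Conclusion.** The point holds as an improvement to a stated method, not as a flaw that invalidates the trial. Adjusting for each limb's baseline would bring the variance of the paired contrast to 0.75-0.95 of the change-score variance for assumed rho of 0.5-0.9, a little less in practice at n = 24. It would also remove the dependence of the estimate on chance left-right differences. If the ANOVA is run on complete cases, using everyone with a week-12 value would avoid an SE excess of about 5-11%, assuming that 5-10% of participants miss each visit independently. With dropout alone, that last gain would be smaller. The figures assume equal variance of the limb difference at weeks 0 and 12; the documents give neither rho nor a missing-visit rate.

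**What to change.** In the Statistical analysis section:

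- Say what arms means, and tabulate baseline lesion extent per limb by treatment.
- Replace the repeated-measures ANOVA with a linear mixed model for the week 4, 8 and 12 values on the per-limb primary outcome scale (BSA, VASI or planimetric area). Fixed effects: ointment, visit, ointment by visit, limb level (upper or lower) and each limb's baseline value. Random effects: participant and limb pair. Let visits on the same limb correlate, since this is how earlier visits inform a missing week 12.
- Use all available visits, and name the week-12 drug-versus-vehicle contrast as the primary test.
- Do not log-transform unless zero areas are handled: the log is undefined for a fully repigmented limb, and log area would depart from the BSA and VASI outcome.

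The cost is a few lines of text and slightly more analysis work in standard software. The variables are already collected.

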#### Primary outcome

The primary outcome of the study was defined as the evaluation of repigmentation of vitiligous lesions achieved after the administration of 1% simvastatin-acid sodium salt or 1% atorvastatin calcium salt ointments compared with vehicle ointments after a 12-week study period. Repigmentation will be assessed according to VASI and BSA scales based on photographs obtained during each visit using planimetry software as mentioned above.

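### The main ANOVA glosses the placebo-drug factor as right versus left side, although side is not treatment in this design, and no named term or contrast is tied to the week-12 change from baseline

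*Protocol article*

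**What the plan says.** The Statistical analysis section of the protocol article gives the main analysis as "analysis of variance (ANOVA) repeated measures with time effect and placebo-drug effect (right versus left side of the body". The next sentence adds: "The statistical significance of differences between groups will be estimated using analysis of contrasts". It names no visit and no particular contrast.

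The allocation is described elsewhere:
- **Intervention:** each participant receives "1% simvastatin-acid sodium salt, 1% atorvastatin calcium salt, and two vehicle ointment-filled containers labeled with a preselected limb", and "application of an active substance to a particular limb is associated with application of the vehicle ointment onto the opposite limb".
- **Design:** the active ointments go on preselected limbs, "taking into account different combinations as presented in Fig. 1".
- **Randomization and blinding:** participants are randomised, and containers are labelled by participant number and limb.

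The target is set in Table 2 (Secondary outcomes section), which lists the primary outcome as repigmentation under simvastatin or atorvastatin "compared with vehicle ointment after a 12-week study period (change from baseline in repigmentation on BSA and VASI scale". The Primary outcome section gives the same time point.

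**The concern.** Two things do not fit together.

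1. **The factor.** If the active ointment is on the right limb for some participants and on the left for others, a right/left variable does not separate drug from vehicle. An analyst who followed the bracket as printed would average drug-minus-vehicle differences with opposite signs.
2. **The tested quantity.** The primary outcome is a change from baseline at one visit. The model sentence lists a time effect and a placebo-drug effect, and the contrasts sentence refers only to differences between groups. Nothing says which term or contrast answers the week-12 question. A placebo-drug effect averaged over visits is a different quantity. A single placebo-drug effect also leaves the two statins unseparated, although each has its own vehicle limb.

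This matters because of how the pilot will be used. The Sample size calculation section uses an interim analysis after the predefined group has been enrolled to set the number of patients needed, and the Discussion uses the results to judge whether larger trials are reasonable. An estimate pulled towards zero would misinform both decisions.

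**Working it through.** The plan gives no alpha, power, effect size or SD for its target of at least 24 patients, so there is no figure of its own to reproduce. The check is algebraic.

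**Inputs from the protocol article:** 24 participants (Sample size calculation); one active and one vehicle limb per pair (Intervention); visits at weeks 0, 4, 8 and 12 (Design). **Assumed:** a true drug-minus-vehicle effect of delta at week 12; the right/left split; the shape of onset.

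**Step 1: literal side coding, one drug.** Let nR participants have the active on the right and nL = 24 - nR on the left. Right minus left has expectation +delta in the first group and -delta in the second, so the expected side effect is delta x (nR - nL)/24.

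| Active on right / left | (nR - nL)/24 | Expected effect |
|---|---|---|
| 12 / 12 | 0/24 | 0 |
| 14 / 10 | 4/24 | 0.17 delta |
| 16 / 8 | 8/24 | 0.33 delta |
| 18 / 6 | 12/24 | 0.50 delta |
| 24 / 0 | 24/24 | delta |

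The full effect is recovered only if the active is always on the right. If sides were allocated by simple randomisation of 24, the central 95% range of (nR - nL)/24 would be -0.42 to +0.42. A simulation at 12/12 (3,000 runs per setting, effect of 1 at week 12, assumed SDs) agreed: the mean side effect was about 0 and the rejection rate was 2% to 5%.

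**Step 2: correct coding, but a treatment main effect over visits.** The main effect is the mean of the drug-minus-vehicle difference over the visits in the model. With d(t) as a fraction of delta:
- Linear onset, raw scores at four visits: (0 + 1/3 + 2/3 + 1)/4 = 0.50.
- Linear onset, change scores at three visits: (1/3 + 2/3 + 1)/3 = 0.67.
- Late onset (0, 0, 0.5, 1): 1.5/4 = 0.375 on raw scores; 1.5/3 = 0.50 on change scores.
- Immediate onset (0, 1, 1, 1): 3/4 = 0.75 on raw scores; 3/3 = 1.0 on change scores.

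On change scores the dilution is therefore milder, and it disappears if the effect is immediate.

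**Step 3: coding by ointment with a week-12 minus week-0 contrast.** The expectation is d(12) - d(0) = delta under every onset shape. In the simulation the mean estimate was 0.99 to 1.01 times delta in all scenarios.

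**The case against.** The strongest reply is that the model term is named the placebo-drug effect and the bracket merely explains it. Because active and vehicle always sit on opposite limbs, every drug-placebo comparison in this trial is a comparison between two sides of one body, and the Design section presents the scheme as allowing a direct comparison of active and placebo. On that reading the factor is the ointment received, and nothing in the article says that data will be pooled by anatomical side. This reading is plausible and may well be what is intended. It does not make the printed wording correct, because right versus left still names a variable that the allocation separates from treatment.

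Second, the article does not say that only a main effect is tested. It does not exclude a treatment-by-time term, and the contrasts sentence could supply the week-12 comparison. A full analysis plan could settle such detail. This stands, and it makes the week-12 part of the point weaker than the coding part.

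A reader might go further and infer that the model cannot estimate the drug effect, or that its power must be very low. The documents do not support either inference. The first requires both the literal coding and a main-effect-only test. The second depends on the response variable. Take 24 pairs, two-sided 5%, compound symmetry and delta set for 80% power on the week-12 change. The three-visit mean change has variance 4/3 x sigma^2 x (1 - rho), against 2 x sigma^2 x (1 - rho) at week 12, where sigma is the SD of the paired difference at one visit and rho its correlation between visits. The noncentrality of 2.926 is then multiplied by sqrt(1.5) and by the dilution factor. That gives 2.39, or 63% power, with linear onset and 3.58, or 93%, with immediate onset, whatever the correlation. Much lower values arise only if raw scores including week 0 are averaged, and the declared outcome is change from baseline.

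**Conclusion.** The point holds as a defect of wording in the sentence that defines the main analysis. The bracket equates treatment with body side, and the allocation makes them different. If it were coded literally, the expected effect would shrink by the factor (nR - nL)/24: to zero at 12/12 and to 0.17 delta at 14/10. The size depends on a split that Fig. 1 would show and that is not available here. It also depends on the literal reading, which the article permits but does not establish.

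The secondary part holds in a limited form. The named effects and the contrasts are not tied to the week-12 change. If a treatment main effect over visits were used, a linearly growing effect would be estimated at 0.5 delta (raw scores) or 0.67 delta (change scores). No claim about the trial's power follows.

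**What to change.** In the Statistical analysis section, replace the bracket with: *ointment allocated to the limb (simvastatin, atorvastatin, vehicle), compared within patient and limb pair*. Keep side (right/left) and limb level (upper/lower) only as nuisance factors. Include a treatment-by-time term. Name as the primary contrast the week-12 change from baseline of each drug against its own opposite vehicle limb, stated separately for simvastatin and atorvastatin.

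The cost is one sentence and a recoding of the treatment variable from the allocation list. No new data are needed, and the change can be made before unblinding.
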